### Sample size

Sample size calculation was based on a 20% improvement in the primary outcome (use of family planning) in the EG compared to CG at 3 months post intervention (T2). A 30% baseline prevalence of family planning use was assumed in the study population based on observed prevalence of family planning use in humanitarian settings, ranging from 7.1% (in Northern Uganda), 25% (among Afghan female refugees in Pakistan), and 34.5% (among Syrian women refugees in Lebanon) (9, 21–23). Allowing for 30% attrition, a sample size of 380 adolescent girls and young women would provide a 90% statistical power to detect a difference of 20% in family planning use at 3 months (from 30% to 50%) using a two-sided 5% significance level. This is equivalent to a relative risk of 1.67. To ensure external validity of the findings, a purposive sampling strategy will be employed, as the Syrian refugee population is not homogenous in Lebanon. Specifically purposive sampling will be used at the level of the site and community outreach, and not at the level of individual participant. Ultimately, the sample will be randomised from chosen PHCs that were selected to be part of this intervention based on specific criteria discussed in an earlier section.

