### Outcome measures

To thoroughly evaluate the impact and effectiveness of the intervention package, we will employ a comprehensive set of questionnaires (incorporating various tools) that will be administered to both the EG and CG. These questionnaires will enable the research team to thoroughly assess the impact of the intervention package on various aspects of the participants' lives, including their well-being and SRH. Refer to Table 1 for a detailed description of each tool and the time of administration.

**Table 1 T1:** Outcome evaluation tools and time of administration.

Outcome	Aim	Tool	Study period			
			Screening	Baseline T0	End-line T1 (8 weeks)	3 months post-intervention T2 (20 weeks)
Participant Inclusion	Inclusion and exclusion	Screening tool (24 questions)	X			
Primary outcome	At least 20% improvement in family planning use among the EG compared to the CG at three months.	Pan Arab-Family Health (PAPFAM) survey (24) (BL: 68 questions; EL: 35 questions; P3M: 37 questions)		X	X	X
Secondary outcomes	Improved well-being among the EG compared to the CG at three months. Multiple dimensions of well-being will be assessed.	Hopkins Symptom Checklist 25 (25 questions) (20, 25, 26)		X	X	X
		WHO-5 Wellbeing (5 questions) (27)		X	X	X
		General Self-Efficacy Scale (10 questions) (28)		X	X	X
		Multidimensional Scale of Perceived Social Support for Arab Women (12 questions) (29)		X	X	X
Intermediate outcomes	Improvement in important mediators in the EG compared to the CG	The Difficulties in Emotion Regulation Scale Short Form DERS-SF (18 question) (30, 31)		X	X	X
		Interpersonal Communication Competency scale (32) (17 question)		X	X	X
		Revised Ways of Coping Checklist (12 questions) (33)		X	X	X
Important variables and confounder	Such as socio-demographic factors; Family planning including other SRH knowledge; Women's reproductive and obstetric history; Gender disadvantage; and previous history of domestic violence	Using questions from the PAPFAM Survey (24).		X	X	X

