#### Primary outcome

The primary outcome of the intervention is to improve contraception/family planning use among the EG compared to the CG at 3 months. This will be measured by the Pan Arab-Family Health (PAPFAM) survey (34). The PAPFAM survey is similar to the well-known Demographic and Health Survey in design but with a focus on family health in the Arab countries. It uses a standardized instrument to collect data mainly on maternal health and reproductive health of women as well as data on child, adolescent, and elderly health. The study will use only relevant sections of the PAPFAM survey, chosen based on their alignment with the study's objectives and research questions. Specifically, questions that assess participants' knowledge, attitudes, and practices related to family planning methods, and utilization of family planning services have been extracted. Other questions relating to socio-economic status, marriage, and STI knowledge have also been extracted.

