### Analysis

A detailed statistical analysis plan will be developed upon completion of the study. The data will first be downloaded from the electronic data collection software, KoBo, and imported into a statistical analysis software.

An Intent-to-treat analysis approach will be adopted to test for significant difference of primary and secondary outcomes over time. For baseline (T0) comparability, descriptive statistics (frequency distributions, means, standard deviations, medians, IQRs) will be obtained for variables collected at baseline outcome evaluation. The Chi-square test and t-test will be used to investigate whether potentially confounding variables are balanced across the two study groups. Any potential bias due to these potential confounders will be evaluated analytically by considering them in the regression model. The internal and external study validity will be evaluated by comparing baseline characteristics of those who completed the study to those lost to follow-up, and by comparing screening characteristics of those included in the study to those eligible but not consented for inclusion in the study.

For primary outcome analysis, binary outcome of FP use (yes/no) will be evaluated between baseline (T0) and endline (T1), and between baseline and 3-month follow-up (T2). To estimate treatment effects, multivariable logistic regression models will be conducted separately for T0-T1 and T0-T2 comparisons to estimate odds ratios of FP use in the intervention group compared to the control group. All models will be adjusted for potential sociodemographic confounders. Given that each model will include one change outcome per participant, within-participant correlation as a result of repeated measures will not arise within individual models.

The primary analysis will be repeated 1- to adjust for potential confounders identified in the bivariate analysis, 2- in the compliant “per protocol” subgroup that attended 6 out of 8 (75%) weekly sessions, 3- to explore the impact of missing data with multiple imputation methods, and 4- to consider the change in FP use from intervention completion to three months.

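### The Analysis section describes the primary dependent variable in two incompatible ways: FP use (yes/no), and an undefined change in FP use that logistic regression cannot take without a coding rule

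*Protocol article*

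**What the plan says.** Three places in the protocol article agree on the outcome. The Primary outcome section sets out to "improve contraception/family planning use among the EG compared to the CG at 3 months". Table 1, under Outcome measures, gives the aim as "At least 20% improvement in family planning use among the EG compared to the CG at three months". The Sample size section rests on the same quantity: "A 30% baseline prevalence of family planning use was assumed", the target is 50% use in the experimental group (EG) at T2, and "a sample size of 380 adolescent girls and young women would provide a 90% statistical power" after allowing for 30% attrition, "using a two-sided 5% significance level". It restates the target as a relative risk of 1.67.

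The Analysis section begins in line with this. It names a binary yes/no FP outcome and multivariable logistic models that estimate odds ratios of FP use, intervention against control. In the same paragraph it frames the evaluation as baseline to T1 and baseline to T2, and then says that "each model will include one change outcome per participant". That statement is its reason for setting aside within-participant correlation. A later list of repeat analyses includes the change in FP use from the end of the intervention to three months. The change variable is never defined, and baseline FP use is not named as a covariate; the models are said to adjust for sociodemographic confounders. The section also says that the detailed statistical analysis plan will be written once the study is complete.

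**The concern.** The two descriptions cannot both be the dependent variable of one model. If the outcome is FP use at the follow-up visit, each woman contributes a yes or a no, and the model can be fitted as written. If it is the change from baseline, each woman contributes one of three values, and someone must decide how to collapse them. The choice alters the question. Started versus everyone else puts women who keep using FP in the same category as women who never use it. Restricting to baseline non-users answers a question about uptake only. Change versus no change counts starting and stopping as the same event.

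At stake is what the primary odds ratio means, and whether its definition is fixed in advance. With the detailed plan placed after study completion, the coding could be settled when several versions are already available to compare.

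**Working it through.** **Step 1. Which quantity was the trial sized on?** Inputs from the Sample size section: 30% versus 50%, two-sided 5%, 90% power, 30% attrition. Allocation is 1:1 (Randomization section).

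- Pooled two-proportion formula: n = [1.96 × √(2 × 0.4 × 0.6) + 1.2816 × √(0.21 + 0.25)]² / 0.20² = 124 per arm.
- With continuity correction: (124/4) × [1 + √(1 + 4/(124 × 0.20))]² = 133.8, so 134 per arm and 268 in total.
- Attrition: 268/0.70 = 383, against 380 stated.
- In reverse: 380 × 0.70 = 266, or 133 per arm. Power is 89.8% with continuity correction and 91.9% without.

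The stated figure reproduces, so the powered quantity is FP use at T2. The implied effects are RR = 0.50/0.30 = 1.67 and marginal OR = (0.50/0.50)/(0.30/0.70) = 2.33.

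**Step 2. What values can a change take?** With use coded 0 or 1, T2 minus T0 is −1 (stopped), 0 (same) or +1 (started). Binary logistic regression needs two levels.

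**Step 3. What would candidate codings give?** Assumptions: 30% use at T0 in both arms; T2 use of 30% in the control group (CG) and 50% in EG; a proportion d of baseline users stopping, equal in both arms. The article gives no value for d. Take d = 10% first.

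- Stopped: 0.30 × 0.10 = 0.03 in each arm.
- Started: EG 0.50 − 0.27 = 0.23; CG 0.30 − 0.27 = 0.03.
- Started versus all others: (0.23/0.77)/(0.03/0.97) = 9.7.
- Started, among baseline non-users: 0.23/0.70 = 0.329 versus 0.03/0.70 = 0.043, OR 10.9.
- Any change versus none: EG 0.23 + 0.03 = 0.26; CG 0.03 + 0.03 = 0.06, OR 5.5.

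**Step 4. What would a baseline-adjusted model of T2 use give?** I fitted logistic regression of T2 use on arm and baseline use to the expected cell proportions. At d = 10% these are 0.90 in both arms for baseline users, and 0.329 versus 0.043 for non-users. The arm OR is 5.6. Averaging the fitted probabilities over the baseline distribution returns 50% versus 30%, that is, a risk difference of 20 points and a risk ratio of 1.67.

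Repeating steps 3 and 4 for other values of d gives these odds ratios:

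| d | T2 use, marginal | Started vs all others | Started, baseline non-users | Any change vs none | T2 use, adjusted for baseline |
|---|---|---|---|---|---|
| 5% | 2.33 | 18.0 | 20.2 | 9.7 | 10.1 |
| 10% | 2.33 | 9.7 | 10.9 | 5.5 | 5.6 |
| 20% | 2.33 | 5.5 | 6.3 | 3.5 | 3.5 |
| 30% | 2.33 | 4.1 | 4.8 | 2.8 | 2.8 |

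Compare within a row. Different rows are different assumed populations.

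**Step 5. Power.** At d of 10%, 20% and 30%, with 133 per arm (93 baseline non-users per arm for the restricted coding), power stays above 95% for all three change codings.

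**The case against.** The best defence is that the change wording is loose drafting. The paragraph names a yes/no outcome and an odds ratio of FP use, both of which match the sizing. The word change appears in a sentence explaining why repeated-measures correlation does not arise, and it may mean only one follow-up value per woman per model. This stands in part: a reader might infer that a change model is definitely planned, and the text does not establish that. It does not remove the problem. The T0-T1 and T0-T2 framing, the reasoning about correlation and the later repeat analysis of change all keep the other reading alive.

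Four further inferences are tempting and not supported.

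- **That the same data could give an odds ratio anywhere from 2.3 to 18.** The 18.0 needs 5% stopping and the 10.9 needs 10%. At 10%, the T2-use and change codings run from 2.33 to 10.9.
- **That any departure from 2.33 shows a wrong analysis.** A sound model adjusted for baseline use also departs from it, at about 5.6 in the illustration, because 2.33 is an unadjusted marginal odds ratio.
- **That baseline non-users will be analysed alone.** The article proposes no such restriction and specifies intention to treat. The codings above are examples of what an analyst might do.
- **That power is lost.** Step 5 shows none under these assumptions.

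Nor is it an error to size on two proportions and test an odds ratio, since both address the same null hypothesis. Detail may fairly be left to an analysis plan, but here the article's own text conflicts on the primary outcome variable.

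**Conclusion.** The point holds as an internal inconsistency in the primary analysis. The dependent variable is described in two ways, only one of which can be fitted as written and matches the outcome defined and sized elsewhere in the article. If a change coding were used, the odds ratio would describe a different quantity. With 10% of baseline users stopping in both arms, it would be 5.5, 9.7 or 10.9 according to the coding, where the marginal odds ratio for T2 use is 2.33.

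That the raw change has three levels and no coding is given needs no assumption. The odds ratios rest on assumed, equal stopping rates and on 30% use at T0 in both arms; they illustrate and do not predict. The harm is to the meaning and pre-specification of the primary estimate, and the sample size is unaffected.

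**What to change.** Delete the change wording and state the primary analysis along these lines: logistic regression of FP use (yes/no) at T2 on randomised arm, in all randomised women, with FP use at T0 and site (the stratification factor in the Randomization section) as covariates. Use the same model at T1 as a secondary analysis. Give the repeat analysis of change from intervention completion to three months an explicit coding.

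Report the standardised (marginal) risk difference and risk ratio with 95% confidence intervals alongside the odds ratio. The baseline-adjusted odds ratio is conditional and cannot be read against the 20-point or RR 1.67 target; the standardised measures can.

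Fix this before outcome data are examined. The cost is a wording change and a small amount of extra analysis. Baseline FP use and site are already collected, and the sample size stays at 380.

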## Methods

### Design

This study will employ a single-blinded community-based participatory research (CBPR) approach to assess the effectiveness of an integrated PSS-SRH intervention on Syrian adolescent girls and young women refugees (aged 15–24 years) residing in vulnerable communities in the Beqaa governorate in Lebanon. The trial consists of two arms: the experimental group (EG) who will receive the PSS-SRH intervention, and the control group (CG) who will receive the same educational material by the end of the study. The primary and secondary study outcomes will be measured at baseline (T0), end-line/post intervention (T1), and at 3-months post-intervention (T2). A comprehensive process evaluation, using a mixed-method study design, will also be conducted alongside the primary intervention outcome evaluation.

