### Randomization

Randomization will be conducted after baseline (T0) assessments are completed and will be stratified by site. Eligible participants will be randomly allocated to EG (intervention group) or CG with a 1:1 ratio. Randomization will be conducting using a computer-generated allocation schema, generated by the study statistician. The randomization schema will use permuted block design with sizes of 4, 6, and 8 blocks in a random mixture, so that treatment allocations are equal after each block size. The young women and adolescents will then be informed of their allocation into either the EG or CG over the telephone.

Participants in the EG will be further divided into subgroups of no more than 12 participants per group. These smaller subgroups facilitate better engagement, interaction, and personalized attention, promoting a supportive and comfortable environment for the participants.

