### Intervention

The WHO PSS-SRH draft intervention package consists of eight modules/sessions focused on SRH education, psychoeducation, and enhancing skills acquisition (specifically around: emotional regulation, communication, problem management, decision-making, and self-efficacy). It is designed to be delivered by trained community paraprofessionals (non-specialists) with at least twelve years of formal education. The draft intervention package will be administered (at the selected PHCs) once a week (for each subgroup) for a duration of 90 min over a total of 8 consecutive weeks. To create a supportive and collaborative environment for the participants in the study, each LWC member will be assigned to an EG subgroup and will attend all their sessions. The involvement of LWC members is expected to build trust and ensure a culturally sensitive approach throughout the intervention delivery. This will play a crucial role in fostering a sense of community among participants, encouraging open discussions, and facilitating the sharing of experiences and ideas. A midwife and a clinical psychologist will also attend all sessions of the intervention to support the paraprofessional when/if needed and to ensure protocol adherence as well as quality and content fidelity. Importantly, the psychologist and midwife will also support participants during the session should they feel distressed, especially when discussing sensitive topics. In such an event, the psychologist or midwife would first attend to the concerns of the participant separately, and if the need arises, they may refer them to relevant care services from professionals within the given PHC or to specialised care outside of the PHC. The intervention delivery schematic (which includes personnel, location, and days of intervention delivery) is displayed in Figure 2.

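### The per-protocol repeat selects on attendance in the experimental arm only, so it is not a randomised comparison and can show an effect when there is none

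*Protocol article*

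**What the plan says.** The Randomization section states: "Eligible participants will be randomly allocated to EG (intervention group) or CG with a 1:1 ratio". Sessions are then delivered to EG subgroups at the health centres, "once a week (for each subgroup) for a duration of 90 min over a total of 8 consecutive weeks" (Intervention). The Design section describes the other arm as "the control group (CG) who will receive the same educational material by the end of the study", so the CG has no weekly sessions to attend during follow-up.

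The Analysis section sets the main approach: "An Intent-to-treat analysis approach will be adopted to test for significant difference of primary and secondary outcomes over time". The primary models are logistic regressions "to estimate odds ratios of FP use in the intervention group compared to the control group", and "All models will be adjusted for potential sociodemographic confounders". Four repeats of the primary analysis follow. The second is in the compliant "subgroup that attended 6 out of 8 (75%) weekly sessions". No criterion for the CG is given. The secondary analyses add an investigation of co-interventions and adherence, with no method named.

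**The concern.** A per-protocol set is normally defined by a rule that can be applied in both arms. Here no CG woman can meet or fail the rule. Two readings are possible. Taken literally, the subgroup contains no CG women and there is nothing to compare. Taken naturally, EG attenders are compared with every CG woman, which selects one arm after randomisation and leaves the other whole.

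On the natural reading, women who manage at least six weekly clinic visits may differ from those who do not in motivation, freedom of movement or family support, and these may also influence FP use. The CG still contains the counterparts of the EG women who were dropped. The estimate then mixes any effect of the package with the difference between attenders and non-attenders. A result labelled as coming from the compliant subgroup is easily read as the effect of receiving the package, which it would not be.

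**Working it through.** **Inputs from the protocol.** Sample size section: 380 women, 30% versus 50% FP use, 90% power, two-sided 5%, 30% attrition. Randomization: 1:1.

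**The plan's own figure.** Two proportions, 0.30 versus 0.50, with continuity correction need 134 per arm, or 268 in total. 268 / (1 − 0.30) = 383, close to the stated 380. (Without the correction: 124 per arm, and 248 / 0.70 = 355.) The sample size does not bear on this point. It is used only for the number of completers: 380 × 0.70 / 2 = 133 per arm.

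**Assumed inputs.** The document gives neither the share of EG women reaching six sessions (c) nor the difference in FP use between attenders and non-attenders. Both are varied below. The true effect is zero and FP use is 30% in both arms.

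**Check 1: a shared latent trait.** A standard normal trait raises the log odds of attendance and of FP use by the same amount per SD. Intercepts are set so that FP use is 30% overall and attendance is c. FP use among attenders comes from numerical integration over the trait. Crude OR = [p_att / (1 − p_att)] / [0.30 / 0.70]. The last column is the chance of a significant result in favour of the EG (pooled two-proportion test, 133 × c attenders against 133 CG women; nominal 2.5%).

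| OR per SD | c | FP use, attenders | Crude OR | False benefit |
|---|---|---|---|---|
| 2 | 60% | 0.333 | 1.16 | about 7% |
| 2 | 70% | 0.325 | 1.12 | about 6% |
| 3 | 60% | 0.366 | 1.35 | about 17% |
| 3 | 70% | 0.349 | 1.25 | about 12% |

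**Check 2: a direct gap.** Let attenders exceed non-attenders by g, so p_att = 0.30 + (1 − c) × g.

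- g = 0: OR 1.00 and false benefit 2.5%. There is no bias.
- g = 20 points, c = 70%: p_att = 0.30 + 0.30 × 0.20 = 0.36. OR = (0.36 / 0.64) / (0.30 / 0.70) = 1.31, false benefit 15.7%.
- Over c = 50–90% and g = 10–30 points: OR 1.05–1.91, false benefit 3.7–55.1%.
- Reversed, g = −20 points, c = 70%: p_att = 0.24. OR = (0.24 / 0.76) / (0.30 / 0.70) = 0.74, so the repeat would suggest harm.

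**Check 3: what an allocation-based estimate does.** In the g = 20, c = 70% case, whole-EG use is 0.70 × 0.36 + 0.30 × 0.16 = 0.30, so the intention-to-treat difference is 0. The complier average causal effect on the risk-difference scale is that difference divided by c: 0 / 0.70 = 0. The spurious 6-point difference disappears.

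The price is precision:

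- Attender subset SE = √(0.36 × 0.64 / 93 + 0.30 × 0.70 / 133) = 0.064, a 95% half-width of about 12.5 points.
- Complier estimate SE ≈ √(2 × 0.30 × 0.70 / 133) / 0.70 = 0.080, a half-width of about 15.7 points.

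**The case against.** The strongest reply is that this is one of four supportive repeats, placed after an intention-to-treat analysis, and that no decision rule hangs on it. That is right, and it limits how much the point matters. A reader might infer that the trial would base scale-up on this estimate. The document does not say so: the Discussion links scale-up to the findings in general, and the Analysis section never presents the repeat as the effect among recipients.

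A reader might also infer that the bias must favour the intervention. Nothing in the document says attenders are likelier FP users, so both direction and size are assumptions.

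The crude odds ratios also leave out the planned adjustment. Table 1 collects gender disadvantage, domestic violence history, FP knowledge, self-efficacy and social support, which overlap with likely drivers of attendance. Using them could reduce the bias. However, the adjustment stated for all models is sociodemographic, and no measured set guarantees comparability once one arm has been selected. Against sampling error the shift is modest: with 93 attenders and 133 controls the SE of the log odds ratio is about 0.29, so odds ratios of 1.12 and 1.25 are shifts of about 0.4 and 0.8 SE.

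The comparator and adherence method might also be settled in the analysis plan, which the article says will be written once the study is complete. The point does not rest on that silence. It rests on the article's stated choice to define the subgroup by attendance alone, which is faulty on either reading.

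Finally, the wording could be read as exactly six sessions. The label compliant and the 75% figure make clear that a minimum is meant. This deserves a wording change and nothing more.

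**Conclusion.** The point holds as a fault in a supportive analysis. The repeat compares self-selected EG attenders with, on the natural reading, the whole CG; randomisation does not protect it and the stated adjustment does not restore that protection. With no true effect, the crude odds ratio would be 1.12–1.35 if 60–70% of EG women attend and one trait carries an odds ratio of 2–3 per SD on both attendance and FP use. The bias vanishes if attendance is unrelated to FP use, becomes small if nearly all EG women attend, and changes sign if attenders are less inclined to use FP. The figures are illustrations before covariate adjustment, not predictions. The intention-to-treat primary result stands untouched. The change is worth making because it is cheap and the replacement keeps the randomised comparison.

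**What to change.** Replace the per-protocol repeat with a complier average causal effect analysis of FP use at three months, using random allocation as the instrument and adjusting for site and baseline FP use. Define adherence as attending at least 6 of 8 sessions, and add a dose version using the number of sessions attended. The CG has no sessions during follow-up, so non-adherence is one-sided, which suits this method.

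State the assumptions:

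- **Exclusion restriction.** Allocation affects FP use only through the attendance measure. The threshold version breaks this if attending one to five sessions has an effect, and is biased away from the null if that effect is in the same direction.
- **Linearity.** The dose version assumes an equal effect for each session.

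Keep any raw comparison of attenders with the CG as descriptive only. Fix this wording before outcome data are seen.

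The cost is a wider confidence interval (about 15.7 against 12.5 points half-width in the example above) and a little more analysis work. No new data are needed, since the planned repeat already requires attendance counts.
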